## Methods

### Trial design

This study is made up of three RCTs and each RCT has two conditions: the KIND Challenge condition and a waitlist control condition. A person enrolled into the KIND Challenge condition will be asked to do acts of kindness at least four times for a duration of 4 weeks and will complete three online assessments. A person enrolled into a waitlist control condition will wait 4 weeks before starting the KIND Challenge and will be required to complete four online assessments. The evaluation of the KIND Challenge will be pre-registered prior to the study launch. Please refer to Fig. 1.

**Fig. 1 Fig1:**
[figure not shown]
CONSORT diagram showing trial design for each country, UA, UK and Australia

### Study setting

This trial will be conducted online in three countries (Australia, United States of America, and the United Kingdom). All measures will be administered through the online survey platform Qualtrics.

### Eligibility criteria

The inclusion criteria will reflect the real-world characteristics of community dwellers who report a need to connect. This includes those aged 18 to 90 years, who are registered Nextdoor users who are willing to commit to the challenge for a specific period of time. Exclusion criteria includes individuals without proficient English reading comprehension skills.

### Who will take informed consent?

Participants are all over 18 years old and can provide informed consent online.

### Intervention – Nextdoor KIND challenge

For those receiving the KIND challenge, they will be asked to nominate different activities they could do over a four-week period to address loneliness in their communities. Because the KIND challenge takes place during the COVID-19 pandemic, participants will be asked to adhere to their state or country’s health department safety guidelines when undertaking these activities. We note here the different types of support that can be selected. Participants are also provided an opportunity to specify their activity in a free text box if none of the presented options were relevant.
Emotional support. Show care and concern for a neighbour (e.g., provide a listening ear, cheer up a neighbour who is down, check in on the welfare of a neighbour)Informational support. Provide advice or helpful information to a neighbour (e.g., where to shop, good doctors in the area, potential job opportunities, gardening tips, etc.)Tangible support. Help a neighbour out (e.g., mow their lawn, take in their garbage bins, offer meals, run errands, bring them groceries, etc.)Belonging support. Contribute to a larger neighbourhood effort, action, or activity (e.g., support a neighbourhood business, share your talents/skills with others, neighbourhood clean-up, volunteering, etc.)Companionship support. Have regular contact with a neighbour (e.g., chat across the fence, street or balcony, call on the phone, etc.)Other. Please specify what you did in the textbox.

The KIND Challenge activities have been selected because they are considered to be positive, engaging, and feasible to the average individual, and draw upon the social support literature to tap into emotional support, informational support, tangible support, belonging support [30], and companionship [31–33]. Participants who are enrolled in the Challenge condition will receive an email reminder to complete the activity weekly till the next post-Challenge assessment. After the four-week period, participants in the KIND Challenge condition will be emailed a link to the post challenge survey. One month after this, they will be emailed a link to the final follow up survey. For those in the KIND Challenge group, there will be three surveys over a two-month period if the participant follows the intended structure of the project.

### Waitlist condition

It will be clearly outlined to participants that the trial involves a waitlist control prior to enrolment, and informed consent will include agreement to undergo a 4-week waitlist period and an additional assessment prior to commencing the KIND Challenge. Waitlist participants will be instructed to continue with their usual activities throughout the waitlist period. Waitlist participants received one email 2 weeks prior to remind them of their upcoming enrolment into the Challenge condition.

### Outcomes

Information about a participant’s demographics, mental health, stress, affect, quality of life, and their perception of the level of community engagement and neighbourhood activity within their own neighbourhood will be collected. The questionnaires are standardised tools that measure physical health, mental health, stress, affect, quality of life, and community engagement. We will also include ratings related to behaviour change. This includes questions to measure the actions selected to interact with others, frequency, and duration of those actions (i.e., dose response), and meaningfulness of those actions. See Table 1 for measures and when they are assessed. We further categorised the outcomes into three sections: intervention primary outcome, intervention secondary outcomes, and implementation secondary outcomes (see Fig. 2).

**Table 1 Tab1:** SPIRIT schedule of enrolment, intervention, and assessments of the Nextdoor KIND Challenge

Time point	Baseline T1	Waitlist T2^a^	Post Intervention T3	1 Month Follow Up T4
Enrolment				
Informed consent	X			
Allocation	X			
Assessments				
Demographic form	X			
UCLA-LS3	X	X	X	X
LSNS-18	X	X	X	X
EUROHIS-QOL-8	X	X	X	X
PHQ-8	X	X	X	X
Mini-SPIN	X	X	X	X
PSS-4	X	X	X	X
PANAS	X	X	X	X
CE	X			
SCS	X	X	X	X
Number of Contacts	X	X	X	X
Neighbourhood Perception of Change	X	X	X	X
Neighbourhood Importance	X	X	X	X
Neighbourhood Modified Social Relationship Index	X	X	X	X
Neighbourhood Conflict	X	X	X	X
Neighbourhood interaction since COVID-19	X	X	X	X
Pre-KIND Challenge Neighbourhood Contact and Previous Kindness activity	X	X		
Nextdoor Platform Activity	X	X	X	X
COVID-19 Social Restrictions	X	X	X	X
Challenge Activity Nomination	X^b^	X		
Post-KIND Challenge Activity			X	
Safety			X	
Post-Kind Challenge Overall Impact			X	
Follow-Up KIND Challenge Activity				X

Note. *UCLA-LS3* refers to UCLA Loneliness - Scale Version 3, *LSNS* refers to Lubben Social Network Scale, *EUROHIS-QOL-8* refers to European Health Interview Survey Quality of Life-8, *PHQ 8* refers to Patient Health Questionnaire-8, *Mini-SPIN* refers to Mini-Social Phobia Inventory, *PSS-4* refers to Perceived Stress Scale-4, *PANAS* refers to Positive and Negative Affect Scale, *CE* refers to Community Engagement, *SCS refers to* Social Capital Scale

^a^Only the waitlist group completed T2

^b^Only those randomised into the Challenge condition will be asked to nominate Challenge activities

**Fig. 2 Fig2:**
[figure not shown]
Nextdoor KIND Challege primary (i.e proximal) and secondary (i.e distal) outcomes

### Intervention primary outcome

#### Loneliness

The UCLA Loneliness Scale - Version 3 (UCLA-LS; [34]) is a 20-item measure employing a 1 (Never) to 4 (Always) ordinal scale. The measure consists of both positively- and negatively- worded items that assess loneliness (e.g., How often do you feel that you are no longer close to anyone?). The UCLA-LS has been shown to correlate negatively with life satisfaction and perceived social support, thus supporting its convergent validity with related constructs.

### Intervention secondary outcomes

#### Social isolation

The Lubben Social Network Scale (LSNS: [35]) is an 18-item scale that assesses the frequency and quality of contact – such as talking about private matters – in an individual’s network. There are three subscales, and each consists of 6 items relating to family, neighbour and friend connections. The scale employs a 0 (none) to 5 (nine or more) ordinal scale and includes 6 items (e.g., How many relatives do you see or hear from at least once a month?). Higher scores indicate lower risk of social isolation. The scale has demonstrated adequate levels of reliability and the proposed clinical cut-points showed good convergent validity [35].

#### Neighbourhood relationship quality and contact

Neighbourhood relationship quality specific variables that we anticipate would be influenced by the KIND Challenge include neighbourhood social cohesion and trust, perception of change, importance, ambivalence, and conflict. Additionally, the number of neighbourhood contact may also increase because of the KIND Challenge.

#### Neighbourhood social cohesion and trust as measured by social capital scale [36]

The Social Capital Scale is a 7-item measure designed to assess social cohesion and trust in a community. The scale was derived from a similar scale used in Sampson et al. [37]. This measure consists of both positively and negatively worded items and is recorded on a 2-point dichotomous format ranging from 0 (strongly disagree or disagree) to 1 (strongly agree or agree). This measure was shown to be a reliable tool to measure social cohesion and trust at a neighbourhood level [37].

#### Neighbourhood perception of change [38]

This question used by a previous study by Bateman and colleagues [38], asks if participants thought their neighbourhood was improving from 1 (improving), 2 (stable) or 3 (declining).

#### Neighbourhood importance [38]

This question used by a previous study by Bateman and colleagues [38], asks how important participants thought it was to know their neighbours from *1 (very important) to 5 (very important)*.

#### Social relationship index - Neighbourhood modified [39, 40]

The 3-item scale was modified from the Social Relationship Index (SRI) which measures both positivity and negativity in relationship ties which can indicate if one has supportive, ambivalent, or aversive ties [39, 40]. We ask participants how helpful, upsetting, and mixed/conflicted their feelings are towards their neighbours when needing advice, understanding, or a favour – rated on a Likert scale from 1 (not at all) to 6 (extremely). Based on these scores and using a threshold model classification, participants are then categorised to either having a supportive, aversive, or ambivalent neighbour relationship.

#### Neighbourhood conflict

Participants will be asked to reflect on their interactions with their neighbours in the past month using a dichotomous yes/no to the following: absence/presence of neighbour conflict, critical comments towards the participant, participant critical of neighbours. Responses will be dichotomously scored as either reporting no instances of neighbourhood contact or reporting at least one instance of neighbourhood conflict. These questions were developed for the study (see Supplementary Table 1 – reference a).

#### Neighbourhood number of contacts

This item asks the number of people the participants know in their neighbourhood, 0 (0–5 neighbours) to 4 (15+ neighbours). This question was developed for the study (see Supplementary Table 1 reference b).

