### Objectives

The overall objective is to examine the social and psychological impact of kindness on a community sample. This will be examined by asking community members within an online social networking platform, Nextdoor, to participate in performing at least four acts of kindness over a four-week period. We refer to this as the Kindness Is Nextdoor (KIND) challenge.

The primary intervention objective of the Nextdoor KIND Challenge is to reduce loneliness in the Nextdoor online communities across three countries (Australia, United States, United Kingdom). We expect significant changes to loneliness. Specifically, it is anticipated that challenge participants will show significantly greater improvement in loneliness compared with the control group, after accounting for known covariates.

A secondary intervention objective of the Nextdoor KIND Challenge is to reduce social isolation risk in the Nextdoor online communities across three countries (Australia, United States, United Kingdom). It is anticipated that challenge participants will show significantly greater reduction in social isolation when compared with the control group.

An additional secondary intervention objective of the KIND Challenge is to improve neighbourhood relationship quality and contact, and we expect significant improvements in neighbourhood ties both in terms of relationship quality and contact. It is anticipated that KIND Challenge participants, compared with the control group, will show greater improvement in neighbourhood relationship quality as measured by social cohesion and trust, perception that their neighbourhood is improving, higher importance around getting to know their neighbours, greater positivity and lower negativity towards their neighbors, and lower neighbourhood conflict. It is anticipated that KIND Challenge participants compared with the control group will also report significantly more neighbourhood contacts compared with the control group.

There are further secondary objectives of the KIND Challenge to improve mental health outcomes, that is lower depression, social anxiety, and stress levels, improve quality of life, and increase positive affect, with those participants in the KIND challenge showing greater positive effects when compared with control participants.

We also anticipate that acts of kindness will be feasible, acceptable, and safe to do for community participants (see apriori in Implementation secondary outcomes section).

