Hypothesis 1 (H1): There will be a reduction in loneliness in participants assigned to the Nextdoor KIND Challenge groups compared to the waitlist control group post the 4-week intervention.Hypothesis 2 (H2): There will be a reduction in social isolation in participants assigned to the Nextdoor KIND Challenge groups compared to the waitlist control group post the 4-week intervention.Hypothesis 3 (H3): There will be an improvement in neighbourhood relationship quality and contact outcomes (a) social cohesion and trust, (b) perception that their neighbourhood is improving, (c) higher importance around getting to know their neighbours, (d) more likely to be classed as having a supportive neighbour network than not, (e) have lower neighbourhood conflict, and (f) increased number of neighbourhood contacts, in participants assigned to the Nextdoor KIND Challenge groups compared to the waitlist control group post the 4-week intervention.Hypothesis 4 (H4): There will be an improvement in mental health secondary outcomes, lower (a) depression and (b) social anxiety, (c) stress, and greater (d) quality of life, and (e) positive affect, in participants assigned to the Nextdoor KIND Challenge groups compared to the waitlist control group post the 4-week intervention.

While it is vital to investigate the impact of KIND Challenge post intervention, it is possible for impact on outcomes to be distal; that is indirect effects caused by changes in proximal outcomes. The KIND Challenge aims to reduce loneliness and social isolation, which may lead to later distal impact on other outcomes. Capturing impact at one-month follow-up after the completion of the KIND Challenge enables modelling the maintenance of intervention effects, i.e., are effects sustained at one-month or are sleeper effects present? In addition to understanding whether effects of the intervention are sustained, it is also important to know whether the intervention itself is sustainable. The KIND Challenge acts are positive, engaging, and feasible to the average individuals, and thus designed to be sustainable.
Hypothesis 5 (H5): The Nextdoor KIND Challenge effects noted in H1–4 above will be maintained at one-month follow-up for the participants randomly allocated to KIND Challenge group.Hypothesis 6 (H6): The KIND Challenge is sustainable, participants assigned to the KIND Challenge will continue engaging in acts of kindness at one-month follow-up.

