#### Post-KIND challenge activity

*Post intervention,* participants will be asked if they completed either their nominated KIND Challenge activity or any KIND Challenge activity over the past month. Type of support can be categorized based on participant selection. Participants can also select “other” activities that were not listed. If the “other” box activity is selected, participants are asked to describe the activity in detail via a free text entry box. Responses in the free text box entry will be coded independently by two research assistants not related to this trial. Inter-rater reliability between coders will be calculated to ensure adequate reliability of categorization. For each activity, participants will be asked how frequently they completed the activity (1 = once to 4 = more than 5 times), the duration of the activity (1 = less than 10 min to 5 = more than 2 h), how connected to others they felt after completing the selected activity (1 = not at all connected to 10 = very connected). They can select more than one activity and will rate each activity according to those scales. If participants have not completed a KIND Challenge activity, an additional multiple-choice question will be included to assess for what reasons the activity could not be completed (e.g., lack of time, that they forgot, illness, work, stress etc). Participants were then asked to reflect on the KIND Challenge overall including how meaningful and safe they found the challenge, how positive they felt after the challenge, and how connected and comfortable they felt towards their neighbours because of the challenge. These questions were specifically developed for the study (see Supplementary Table 1 - section c).

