### Secondary outcomes analysis

The above ITT analysis using linear multiple regression modelling in Mplus 8.3, will be repeated for the secondary outcome of social isolation (H2) and the neighbourhood relationship quality outcomes H3 (a) social cohesion and trust (measured using the Social Capital Scale) at post 4-week intervention. For outcomes (b) perception that their neighbourhood is improving (categorised at improving, stable or declining), and (d) supportive, aversive, or ambivalent neighbour network classification, because those are categorical data, we will use a multi-nominal regression. Outcomes (c) higher importance around getting to know their neighbours (high and low importance), (e) neighbourhood conflict (no neighbourhood conflict and instances of neighbourhood conflict), and (f) number of neighbourhood contacts (0–5 and 6+ neighbourhood contacts) are dichotomous categorical data so we will use a binominal regression to explore ITT effects. Similarly, for all mental health secondary outcomes at post 4-week intervention, H4 (a) depression (b) social anxiety, (c) stress, (d) quality of life, and (e) positive affect, measured using the PHQ-8, Mini-SPIN, PSS-4, EUROHIS-QOL-8, and PANAS-PA respectively. The same model building approach will be adopted as in H1.

To model whether effects are maintained for all outcomes (H5) in the participants assigned to the KIND Challenge group, a series of within-group ANCOVAs will be run. Differences in baseline (T1), post-intervention (T2), and one-month follow-up (T3) outcomes will be analysed for both primary and secondary outcomes. A model building approach will be taken controlling co-variates outlined above for H1–4. The sustainability of the intervention (H6) will be explored to determine if the participants assigned to the KIND Challenge group continue with acts of kindness. Both the frequency and duration of KIND acts completed in the one-month follow-up, and the level of engagement for each type of activity completed (i) emotional support, (ii) tangible support, (iii) informational support, (iv) belonging support, and (v) companionship support will be analysed. A series of within-group ANCOVAs will be run using the frequency and duration of KIND acts completed post 4-week intervention and one-month follow-up, to determine if engagement is sustained.

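### The neighbour-contacts item pools 0–5 people in its lowest band and is analysed as 0–5 versus 6+, so H3(f) registers a gain only when a participant passes five

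*Protocol article*

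**What the plan says.** Under the heading Neighbourhood number of contacts, the protocol article describes the measure: "This item asks the number of people the participants know in their neighbourhood, 0 (0–5 neighbours) to 4 (15+ neighbours"). Table 1 schedules it at baseline, at the end of the waitlist period, post-intervention and at one-month follow-up.

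The item serves H3(f) in the Objectives section, which predicts "increased number of neighbourhood contacts, in participants assigned to the Nextdoor KIND Challenge groups" relative to the waitlist group.

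The Secondary outcomes analysis section fixes how it is analysed: "f) number of neighbourhood contacts (0–5 and 6+ neighbourhood contacts) are dichotomous categorical data so we will use a binominal regression".

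The Objectives section gives the dose: participants are asked to "participate in performing at least four acts of kindness over a four-week period". The article gives no expected gain in the number of neighbours known and no expected baseline distribution. The section introducing neighbourhood relationship quality and contact says only that contacts may rise.

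**The concern.** The hypothesis is about an increase in a number, but the instrument cannot tell knowing nobody from knowing five people. A participant who knew no neighbours and now knows four is recorded as unchanged. This happens at collection, so no later analysis of the stored bands can recover it.

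The planned analysis adds a second loss. With one cut between five and six, movement among people who already know six or more also disappears, even where the item recorded it in a higher band.

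At stake is sensitivity on one secondary outcome, most of all for participants who know few neighbours. The design does not inflate false positives. The risk is that a null result on H3(f) is reported as no increase in contacts when small increases occurred below the cut.

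**Working it through.** **Plan's own figure.** None is given for this outcome. The only design figure is the minimum detectable effect size of .14 for loneliness. It reproduces with 1,500 participants, 1:1 allocation, 20 covariates, pre-post correlation 0.35, power 0.80 and two-sided alpha 0.05 (sidedness assumed): 2.803 × √[(1 − 0.35²) / (0.25 × 1500)] = 0.136. It does not bear on the contacts item.

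**Which gains are seen.** From the article: lowest band 0–5, analysis cut between 5 and 6. A person starting at s (0 to 5) who gains g people is recorded as changed only if s + g ≥ 6. If s is uniform on 0–5 (assumption), the share missed is (6 − g)/6.

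| Gain | Starting counts that cross | Starting counts that do not | Share missed |
|---|---|---|---|
| 1 | 5 | 0–4 | 83% |
| 2 | 4, 5 | 0–3 | 67% |
| 3 | 3–5 | 0–2 | 50% |
| 4 | 2–5 | 0, 1 | 33% |
| 5 | 1–5 | 0 | 17% |
| 6 | 0–5 | none | 0% |

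**Power within the lowest band (illustration).** Assumptions not in the article: n per arm in the band, starting counts uniform on 0–5, Poisson gains with means m₁ and m₀, and counts reported without error. For small gains, the probability of leaving the band is close to m/6.

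With means 1.0 versus 0.7 and n = 150:
- On the count: standard error √[(1.0 + 0.7)/150] = 0.106; 0.3/0.106 = 2.82; power Φ(2.82 − 1.96) ≈ 0.81.
- On leaving the band: 0.167 versus 0.117; standard error √[(0.167 × 0.833 + 0.117 × 0.883)/150] = 0.040; 0.05/0.040 ≈ 1.25; power Φ(1.25 − 1.96) ≈ 0.24. Simulation with a pooled two-proportion test gives 0.22.

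Other inputs:

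| n per arm in band | Mean gains | Power on count | Power on leaving band |
|---|---|---|---|
| 150 | 1.0 vs 0.7 | 0.81 | 0.22 |
| 375 | 1.0 vs 0.7 | 0.99 | 0.51 |
| 150 | 0.5 vs 0.2 | 0.99 | 0.46 |
| 150 | 2.0 vs 1.5 | 0.90 | 0.35 |
| 150 | 2.0 vs 1.0 | 1.00 | 0.93 |

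The 375 row is half of 750 per arm, the planned 1,500 per country split 1:1.

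**Power of the planned 0–5 versus 6+ comparison in one country (illustration).** Assume 750 per arm, half of participants in the lowest band and evenly spread, half of those on the Challenge gaining g people, and no change in controls. The 6+ proportion on the Challenge is then 0.5 + 0.5 × 0.5 × g/6: 0.542, 0.583 and 0.667 for g = 1, 2 and 4, against 0.500. Power is about 37%, 90% and close to 100%. The split is weak for small gains and adequate for large ones.

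**The case against.** **The effect size is not the article's.** This stands. Four acts is a minimum, and each activity can be reported with a frequency scale covering "how frequently they completed the activity (1 = once to 4 = more than 5 times"). Acts may also be repeated with one person, since one option is to "Have regular contact with a neighbour". Nothing links four acts to any number of newly known neighbours. Repetition with one neighbour makes small gains plausible, but that is a judgement.

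**A reader might infer that gains among the least connected cannot be recorded at all.** The arithmetic does not support this. At a gain of four, four of the six starting values in the lowest band cross. Nor is six the smallest detectable gain: it is the gain at which everyone in the band crosses, and a gain of one is seen for people starting at five.

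**A reader might take one power pair as the trial's power.** The pair 0.81 versus 0.22 needs 150 per arm in the band and gains of 1.0 versus 0.7, neither of which is in the article. The comparison also treats self-reported counts as exact, which favours the numeric item.

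**Another measure covers this ground.** The LSNS-18, given at the same visits, has six neighbour items scored from none up to nine or more. It can pick up change at the low end, but it is the social isolation measure for H2 and not the endpoint of H3(f). It mitigates the problem without curing it.

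**The target group is not defined by isolation.** This also stands: eligibility sets no loneliness or isolation threshold and recruitment is open to all kinds of users. How many participants sit in the lowest band is unknown.

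**The item's middle bands are in Supplementary Table 1, which is not shown.** They lie above the 0–5 code and cannot resolve it.

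**Conclusion.** The point holds as a loss of sensitivity on a secondary outcome. The response format and the analysis cut, both fixed in the article, mean that H3(f) registers a gain only on passing from five or fewer contacts to six or more. Under a uniform baseline on 0–5, gains of 1 to 4 people are missed for 83% down to 33% of the lowest band, and gains by those already at six or more are discarded by the split.

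Banding lost power in every scenario tried, but the amount runs from severe (0.81 to 0.22) to slight (1.00 to 0.93), depending on gain and baseline inputs that the article does not give. The documents do not support saying that the outcome is unmeasurable or that the trial is underpowered for it. They do support saying that a null on H3(f) would be uninformative about small gains among people who know few neighbours.

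**What to change.** **If the item can still be changed.** Ask for the number of neighbours known as a numeric entry, or as single values 0, 1, 2, 3, 4, 5 followed by bands, in the same form at every visit. Analyse it as a count (for example negative binomial regression) or as an ordinal outcome, adjusted for the baseline value, in place of the 0–5 versus 6+ split. The cost is one change of response format in Qualtrics and a revised sentence in the analysis section. The downside is some recall error in large counts.

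**If the data are already banded**, which the dates under Trial status (July 2020 to January 2021) make likely. Use all the bands in an ordinal model adjusted for the baseline band. This recovers movement across boundaries above six but nothing within 0–5. State in the report that H3(f) cannot detect gains that leave a participant at five or fewer contacts, and that a null result must not be read as no increase. The LSNS-18 neighbour items could be reported alongside as supporting evidence, labelled as belonging to H2. This costs only a change of model and one sentence of interpretation.
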